**Methods:**

A cluster randomized controlled trial (RCT) with students randomized to HL or to care as usual will be conducted. Pre-vocational students in their first or second year (aged 12 to 14) will participate in the study. Subjects in both conditions will complete assessments at baseline and at 3- and 6-months follow-up. The primary outcome will be depressive symptoms using the Center for Epidemiologic Studies Depression Scale (CES-D) at 6-months follow-up. Secondary outcomes are well-being using the Warwick-Edinburgh Mental Well-Being Scale (WEMWBS) and life satisfaction (Cantril Ladder) measured at 6-months follow-up. Alongside the trial, an implementation study will be conducted to evaluate the implementation of HL, using both quantitative and qualitative methods (interviews, survey, and classroom observations).

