### Aim

The main objective of the RCT is to investigate the effectiveness of HL in terms of a reduction of depressive symptoms in pre-vocational students aged 12 to 14 after 6 months compared to care as usual. We hypothesize that adolescents who participate in the HL-program will have lower levels of depressive symptoms at 6-months follow-up than adolescents who do not participate. Secondary outcomes that will be investigated are well-being and life satisfaction. We hypothesize that students who receive HL report higher levels of well-being and life satisfaction than students who do not receive HL.

In addition, we want to identify potential mediator factors that increase or decrease the intervention’s effectiveness. We will investigate school and class climate indicators. We hypothesize that students who receive HL will report higher levels of classmate support, teacher support, and school connectedness, and lower levels of bullying, which will lead to a reduction of depressive symptoms among students.

A secondary aim of this study is to evaluate the implementation process of the HL-program, from the perspectives of intervention recipients, implementers, and the broader stakeholders at the school level (e.g. teachers). The aim of this evaluation will be to understand how the intervention was implemented and what factors might be important when sustaining or expanding the HL-program over time or in new schools.

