### Design of the RCT

The effectiveness of HL will be tested within a cluster RCT with two conditions: an intervention condition (receiving HL during the study) and a control condition (care as usual, HL will be delivered after the final follow-up assessment). Participating classes will be randomly assigned to either the intervention or the control condition and will be equally distributed across the two conditions within each schoolyear. This design is chosen to avoid a skewed distribution of participants over the two conditions due to school effects. The randomization will be conducted by an independent statistician. Three assessments will be performed in the study: T0 (pre-test, before the start of HL in intervention group); T1 (3-months follow up); T2 (6-months follow-up).

Data will be collected in two cohorts: the first cohort is planned in the 2021-2022 school year and the second cohort is planned in 2022-2023 school year.

See Fig. 2 for the flowchart of the study and Table 1 for an overview of the schedule of enrolment, interventions, and assessment.

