#### Statistical analyses

All statistical analyses will be conducted in R [48] by an independent researcher. Reporting of the results will be conducted in accordance with the (extended) CONSORT statement [23]. Analyses will be conducted based on the intention-to-treat (ITT) principle. The primary ITT analyses will be performed using linear mixed models, which adequately deal with missing at random data and can be used to account for the nested structure of the data; students nested within classes and repeated assessments nested within students [49]. Time, condition, and time by condition interactions will be specified as fixed effects to examine the effectiveness of the intervention on continuous primary and secondary outcomes. Baseline scores of the corresponding outcome will simultaneously be entered as fixed factors in the model to account for baseline imbalances. In accordance with the CONSORT statement [23], it will not be explicitly tested whether conditions statistically differ in their baseline characteristics. Hence, the decision whether models will be adjusted for additional covariates will not be based on whether statistical differences in these covariates exist at baseline. Instead, models will primarily be reported that are not adjusted for additional covariates. In an additional sensitivity analysis, it will be examined whether adjusting these models for the following baseline variables substantially changes conclusions drawn from the analyses: gender, age, immigration background, depressive symptoms, well-being, and life satisfaction. Post-hoc tests will be conducted to examine between-group differences at each timepoint using analyses of covariance (ANCOVA), including baseline scores as covariate. Based on estimated marginal means and corresponding standard errors from linear mixed models, between-group effect sizes at each timepoint will additionally be expressed as Cohen’s *d* with 95% confidence intervals.

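### The 6-month CES-D difference is the trial's question, but the analysis section never names that contrast as the primary test

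*Protocol article*

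**What the plan says.** The question is fixed at one time point. The abstract states: "The primary outcome will be depressive symptoms using the Center for Epidemiologic Studies Depression Scale (CES-D) at 6-months follow-up". The Aim section expects that adolescents who take part in the programme "will have lower levels of depressive symptoms at 6-months follow-up than adolescents who do not participate". The Sample size section tests d = 0.20 at 6 months, two-sided 5%, with 80% power. Assessments are at T0, T1 (3 months) and T2 (6 months).

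The Statistical analyses section describes a linear mixed model with students nested in classes and assessments nested in students. Its fixed effects are introduced by: "Time, condition, and time by condition interactions will be specified as fixed effects to examine the effectiveness of the intervention". The next sentence adds: "Baseline scores of the corresponding outcome will simultaneously be entered as fixed factors in the model to account for baseline imbalances". It does not say whether the T0 score is also one of the repeated outcomes.

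The comparison at a given time point then appears twice:
- as a test: "Post-hoc tests will be conducted to examine between-group differences at each timepoint using analyses of covariance (ANCOVA), including baseline scores as covariate";
- as an estimate: from the mixed model's marginal means, "between-group effect sizes at each timepoint will additionally be expressed as Cohen’s" d with 95% confidence intervals.

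Neither is called the primary analysis.

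**The concern.** A reader looking for the confirmatory test finds three candidates: the interaction in the mixed model, the T2 difference from that model's marginal means, and a separate ANCOVA at T2. The sentence that speaks of effectiveness is the one that lists the interaction. The comparison on which the trial was sized is labelled post-hoc. That label could suggest that the time-point comparisons follow only after a significant interaction.

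The candidates answer different questions and have different error rates. If the interaction serves as the test, a benefit that is present at 3 months and held to 6 months can go undetected, and a benefit that has vanished by 6 months can be declared significant. Because the text does not settle the matter, the choice could be made after the data are seen.

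**Working it through.** **Inputs from the Sample size section.** d = 0.20; two-sided 5%; 22 students per class; ICC 0.02; cluster size variation 0.17; baseline correlation 0.30; 315 per condition; 40% non-consent, so about 22 × 0.6 = 13.2 consenting students per class.

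**Assumptions, not in the document.** T1-T2 correlation 0.3 to 0.7; T0 correlates 0.30 with both T1 and T2; outcome SD 1; complete data.

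**The plan's own figure.** 315 could not be reproduced: 392.4 × 1.433 × 0.91 ≈ 512 per arm, where 1.433 is the design effect at 22 per class and 0.91 = 1 − 0.30². That is a separate issue. Here 315 serves only as a common size for comparing tests.

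**1. The contrast the trial is about: baseline-adjusted difference at T2.**
- Design effect at 13.2 per class: 1 + ((0.17² + 1) × 13.2 − 1) × 0.02 = 1.2516.
- SE = √(2 × 1.2516 × 0.91 / 315) = 0.0850; 0.20 / 0.0850 = 2.35; power about 65%.
- Simulation (24 classes of 13 per arm, 4,000 runs per scenario, class effects constant over time) gave 66-68% whatever the T1 effect, with type I error of about 5%.

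**2. Interaction, T0 as covariate only (outcomes T1 and T2).** The interaction estimates d(T2) − d(T1). With class effects constant over time, SE = √(2 × 2(1 − ρ) / 315), where ρ is the T1-T2 correlation: 0.0943, 0.0797 and 0.0617 for ρ = 0.3, 0.5 and 0.7.

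| True d at T1 | True d at T2 | Interaction rejects |
|---|---|---|
| 0.20 | 0.20 | about 5% |
| 0.10 or 0.30 | 0.20 | 19-37% |
| 0 | 0.20 | 56-90% |
| 0.30 | 0 | 89-100% (simulated) |

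The first row is a sustained benefit at the planned size; the last is no benefit at 6 months.

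**3. Interaction, T0 also an outcome.** A covariate that is constant within a student cannot alter a within-student contrast, so the T2−T0 interaction is a plain change-score comparison.
- Variance factor: 2(1 − 0.30) = 1.40, against 0.91 for the adjusted T2 contrast (1.40 / 0.91 = 1.54, or 54% larger).
- Class effects constant over time, so that they cancel: SE = √(2 × 1.40 / 315) = 0.0943; power 56%.
- Full design effect on the change score (class effects weakly correlated over time): SE = √(2 × 1.2516 × 1.40 / 315) = 0.1055; power 47%.
- The single baseline slope, pooled over three occasions in a random-intercept model, is (1 + 0.30 + 0.30) / 3 = 0.53. Marginal means at T2 would then be corrected for baseline imbalance by 0.53 per unit instead of 0.30.

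**4. ANCOVA at T2, if class were ignored.** The test statistic is inflated by √1.2516 = 1.119. The true size of a nominal 5% test is the two-sided normal tail beyond 1.96 / 1.119 = 1.75, about 8%.

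**The case against.** The strongest reply is that the text never makes the interaction the primary test. It lists three fixed effects of one model, and that model contains the T2 difference (condition plus interaction at T2). The article commits to reporting this difference with a 95% confidence interval, so a sustained benefit would not be hidden from the reader. This stands, and it rules out the claim that the plan tests the wrong hypothesis.

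It may also be said that the model is sound. A reader might infer that entering baseline as a covariate is itself a mistake, or that the model fails on either reading. The document does not support that. With T0 as covariate and T1 and T2 as outcomes, the adjustment is standard. This is also the more natural reading, since an ANCOVA on T0 adjusted for T0 would be meaningless. The article does not state it, however, so the losses in step 3 of the working remain possible, not established.

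A reader might also infer a badly inflated type I error for the interaction. With T0 as an outcome and a random-intercept model, simulation gave 5.1-7.7% with class effects constant over time, and about 10% with class effects correlated 0.3 over time. Neither that correlation nor a random-intercept-only structure is in the article, so no weight is placed on these figures. Likewise, the article does not say that the ANCOVAs will ignore class; it only fails to mention class there.

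Finally, covariance details belong in a fuller plan. That is fair, but which contrast answers the primary question is not such a detail. The article does address it, and does so by attaching effectiveness to the model terms and the post-hoc label to the time-point tests.

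**Conclusion.** The point holds as a failure to tie the primary test to the stated question. It does not hold as a claim that the interaction has been designated as primary or that the 6-month effect is unobtainable.

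The consequence is conditional on what the analyst does. Taking the interaction as the test costs almost all power for a sustained effect if T0 is only a covariate, and roughly 9 to 18 percentage points of power (65% down to 56% or 47%) if T0 is also an outcome. The first result depends on the unknown 3-month effect and T1-T2 correlation, the second on how class effects correlate over time. The slope of 0.53 assumes a random-intercept model with complete data. The 8% size for an ANCOVA without class assumes ICC 0.02 and about 13 students per class. If the T2 contrast from the clustered model with T0 as covariate only is used, none of these losses arises.

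**What to change.** Add to the Statistical analyses section, before any outcome data are analysed:
- the outcomes in the mixed model are T1 and T2, and T0 enters only as a covariate;
- the primary test is the baseline-adjusted condition contrast at T2, with its 95% confidence interval, from the mixed model that includes class;
- the T1 contrast comes from the same model and replaces the separate post-hoc ANCOVAs;
- neither contrast is conditional on the interaction being significant;
- the same form applies to WEMWBS and the Cantril Ladder.

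A baseline-by-time term, class effects that vary over time and an unstructured student-level covariance are optional refinements. The cost is a few sentences, with no change to design, data collection or sample size.

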##### The classroom lessons

The first lesson focuses on the introduction of HL and on the subject happiness. The goal of this first lesson is to encourage a discussion about feeling happy or unhappy, familiarize students with different aspects of happiness, discuss the difference between happiness and being lucky, and to break the taboo about feeling unhappy or down. In this context, engaging group assignments and discussions take place.

In the second lesson, students will learn more about the things that might make them happy and the relationship between feelings, thoughts, and actions. In addition to a class-based exercise, students are asked to complete the online HL-questionnaire. This is a questionnaire on demographics (i.e., gender, age), their own health, family situation (i.e., their family’s’ financial situation, and their family members’ (mental) health status), a depression scale, life satisfaction scale, and a well-being scale. After students complete the HL-questionnaire, they will start the e-learning module which contains videos, animations, and fun and engaging exercises. The e-learning module helps students to improve their mood and to practice the skills with their own feelings, thoughts, and actions.

The third lesson starts with an exercise where the HL-trainer describes different situations (e.g., when students receive the results from a test or students have to give a presentation). Students are asked to describe their feelings for each situation (i.e., being angry, sad, scared, or happy). The lesson also contains an e-learning module with the same elements as the second lesson but is focused on: (1) problem solving, (2) communication tips that help students maintain positive relationships with friends, parents, teachers, (3) the importance of helping others, and (4) thinking about their future dreams and how they can achieve these.

The fourth and final lesson includes a recap of what students have learned so far. In addition, it focusses on the relationship between thoughts and feelings and how students can challenge negative thoughts and change them into more helpful thoughts. Students are also asked to fill in a short evaluation questionnaire about the program. The duration of each lesson is approximately 45 minutes.

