#### Sample size

The sample size is based on the main outcome: depressive symptoms in pre-vocational students in first and second year classes. Based on a meta-analysis by Stice et al. [24], we assume an effect size of *d* = 0.20. Thus, we want to test the hypothesis that we will find an effect of *d *= 0.20 (or larger) at 6 months follow-up. This will be tested at a two-sided significance level of 5% and a power of 80%. Accounting for the clustering in the data with 22 students on average per class, an intraclass correlation of 0.02, a cluster size variation of 0.17 and a baseline correlation of 0.30, we need *n* = 315 students in each condition. Furthermore, we expect that approximately 40% of parents and/or students will not provide informed consent. In order to secure the needed sample size, the aim is to sample 525 students per trial. Assuming an average of 4 classes of 22 students per school (divided across intervention and control condition), this will require 48 classes from about 12 schools.

The sample size calculation was performed in Stata version 14.2 statistical software package using the clustersampsi-procedure. The intraclass correlation coefficient (ICC) of 0.02 was based on two studies: the Dutch Health Behaviour in School-aged Children Survey (HBSC) [32], where the ICC on the emotional scale within the Strengths and Difficulties Questionnaire (SDQ) was 0.008 (95% CI: 0.003-0.02) and a large European study where the ICC’s for depressive mood varied across countries from 0.01 to 0.07 [33].

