#### Data collection

Data will be collected through an online questionnaire and students’ self-reports. Students will use their personal HL-accounts (created by the HL-trainer) to gain access to the questionnaires. Data for each assessment and in both conditions will be collected during a regular classroom lesson. At the end of the recruitment session, the research assistant will ask all students to fill in the HL-questionnaire as part of the HL-program. For those participating in the study this data will serve as the baseline measurement (T0) for the RCT. For research purposes, the HL-questionnaire is administered before the start of the HL instead of the second lesson. For the second (T1) and third assessment (T2), teachers are approached to collect and administer the questionnaires in their classes. The duration of each questionnaire will be approximately 15 minutes.

Data collected for research purposes will be stored in a database. For each individual student, a unique respondent number will be used. Students’ names and email addresses will be stored in a separate database, which is only accessible for the data manager of the project.

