#### Measures

##### Demographic characteristics

*Demographic characteristics* include gender, birth month and -year and immigration background. Immigration background is assessed by asking the students to indicate their own and both of their parents’ country of birth. Students are considered to have an immigration background if they or at least one of the parents was born in another country then the Netherlands. Students’ educational level is collected via the school.

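### Five collected, pre-listed baseline variables are kept out of the primary CES-D model, which already adjusts for baseline CES-D; making the fuller model primary would be a small, cheap gain in precision and robustness

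*Protocol article*

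**What the plan says.** All quotes are from the protocol article.

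- **Primary model (Statistical analyses).** A linear mixed model with time, condition and their interaction. It also carries the baseline value of the outcome analysed: "Baseline scores of the corresponding outcome will simultaneously be entered as fixed factors in the model to account for baseline imbalances".
- **Further covariates.** The choice to adjust "will not be based on whether statistical differences in these covariates exist at baseline". The article then states that "models will primarily be reported that are not adjusted for additional covariates".
- **Sensitivity analysis.** The models are refitted with a closed list of baseline variables: "gender, age, immigration background, depressive symptoms, well-being, and life satisfaction".
- **Availability.** Demographic characteristics "include gender, birth month and -year and immigration background". The HL-questionnaire holds "a depression scale, life satisfaction scale, and a well-being scale" (The classroom lessons), and under Data collection "this data will serve as the baseline measurement (T0) for the RCT".
- **Planning value (Sample size).** The calculation uses "a cluster size variation of 0.17 and a baseline correlation of 0.30".

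**The concern.** The article moves from a correct principle to a conclusion that does not follow from it. Choosing covariates by baseline significance tests is poor practice. A list fixed in advance avoids it just as well as having no further covariates. No other reason is given for leaving the list out of the headline model.

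Two things are at stake. The first is precision: on the planning correlation, baseline CES-D accounts for only a small part of follow-up variance, so other prognostic variables have room to help. The second is robustness. Whole classes are randomised, about 24 per arm, so the mix of students can differ between arms by chance. Consent letters go out to parents of both groups, which suggests (an inference, not a statement in the article) that allocation precedes consent. With about 40% non-consent expected, the consenting students could then also differ between arms. Adjustment for measured covariates reduces the effect of either kind of difference.

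The article offers some grounds for thinking the variables prognostic. Background calls low well-being a risk factor for depression, and Statistical analyses says that adolescents with ethnic minority backgrounds report more mental health problems.

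**Working it through.** **Inputs from Sample size.** d = 0.20, two-sided 5%, power 80%, 22 students per class, ICC 0.02, cluster size variation 0.17 (read as a coefficient of variation), baseline correlation 0.30, 315 per condition, 48 classes, 40% non-consent.

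**The plan's own figure.** Individual randomisation needs 392.4 per arm. The design effect is 1 + ((0.17² + 1) × 22 − 1) × 0.02 = 1.433. The baseline factor is 1 − 0.30² = 0.91. The product is 392.4 × 1.433 × 0.91 = 511.7, so 512 per arm. The stated 315 is not reproduced; on these inputs it gives about 59% power. The step 315 / 0.60 = 525 does reproduce. The mismatch is a separate matter. It matters here only for the starting power, so both starting points are shown.

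**Starting variance.** The baseline score explains 0.30² = 9%, leaving 0.91.

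**Gain from the further covariates.** Let q be the additional share of total outcome variance they explain. The article gives no value, so q is an assumption. The design effect is held fixed.

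- SE ratio = √((0.91 − q) / 0.91)
- Equivalent sample-size ratio = 0.91 / (0.91 − q)
- Power from an 80% start = Φ((1.960 + 0.842) / SE ratio − 1.960)

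| q (assumed) | Variance left | SE ratio | Sample-size ratio | Power from 80% |
|---|---|---|---|---|
| 0.01 | 0.90 | 0.994 | 1.011 | 80.4% |
| 0.02 | 0.89 | 0.989 | 1.022 | 80.9% |
| 0.03 | 0.88 | 0.983 | 1.034 | 81.3% |
| 0.05 | 0.86 | 0.972 | 1.058 | 82.2% |
| 0.10 | 0.81 | 0.943 | 1.123 | 84.4% |

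At 315 per arm, the last three ratios are worth about 11, 18 and 39 students per arm (315 × 0.034, 0.058, 0.123). From the recomputed 59% power, q = 0.03, 0.05 and 0.10 give about 61%, 62% and 64%.

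**Size of chance imbalance, one example.** Take gender at 50%, 315 per arm, and an assumed ICC of 0.02 for gender. The standard deviation of the between-arm difference in proportion is √(2 × 0.25 / 315 × 1.433) = 0.048. If gender shifted the outcome by 0.3 SD (an assumption), the resulting shift in the estimate would have a standard deviation of 0.3 × 0.048 = 0.014, against a target of 0.20. An ICC of 0 to 0.05 gives 0.012 to 0.017. This covers chance only, not differential consent.

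**Cost in degrees of freedom.** 48 × 22 × 0.60 = 633.6, so about 630 students in 48 classes. A handful of student-level terms costs little.

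**The case against.** The strongest reply is that nothing here is wrong. The article names one primary model, adjusts it for the baseline outcome score, rejects test-driven selection, and pre-specifies a fuller sensitivity analysis. Either order of the two models is legitimate. That stands, and it limits the point to a suggested improvement.

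A reader might infer that the primary analysis is unadjusted and open to imbalance in general. The article does not support this: the baseline outcome score, normally the most useful covariate, is in the model for exactly that purpose. For well-being and life satisfaction as outcomes, their own baselines are in too.

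The design also helps. Sample size has the classes within a school divided between the arms, and Design of the RCT spreads classes equally within each school year to limit school effects. Differences in composition between schools are therefore partly balanced. Chance differences between classes are random error, not bias.

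The evidence for prognostic strength is thin. For gender and age, Statistical analyses speaks of who may benefit more, which is effect modification; adding a main effect gains precision only if the variable predicts outcome. Age spans only 12 to 14. Baseline well-being and life satisfaction probably overlap with baseline CES-D. All of this shrinks the likely gain.

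The simpler model also saves something: it avoids handling missing covariates, notably parental country of birth. But the sensitivity and moderator analyses must handle the same variables anyway. How a substantial change in conclusions would be judged is detail that a separate analysis plan may hold, and it is not part of this point.

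**Conclusion.** The point holds as a minor efficiency and robustness improvement. The article gives no reason that requires keeping a fixed, collected list out of the primary CES-D model. In a linear model, adding these covariates leaves the target mean difference unchanged. For the secondary outcomes the point reaches only the listed variables other than the outcome's own baseline.

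The benefit is modest: a standard error lower by about 1.7%, 2.8% or 5.7% if the variables explain a further 3%, 5% or 10% of variance, and under one point of power at 1% to 2%. These shares are assumptions, and the 9% for baseline CES-D is a planning value. The arithmetic also assumes an unchanged design effect.

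Two stronger readings should be resisted. The present hierarchy does not bias the result by itself. Nor would the extra covariates repair the sample size: for 315 per arm to give 80% power on the other stated inputs, total explained variance would need to be about 44% (a correlation of about 0.66), far beyond what is assumed here.

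**What to change.** Before outcome data are seen, exchange the two models in Statistical analyses.

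- **Primary:** the mixed model with gender, age, immigration background and baseline CES-D, WEMWBS and Cantril score, for each outcome.
- **Sensitivity:** the same model with only the baseline score of the outcome analysed.
- **Missing baseline covariates:** one simple rule, stated in advance and applied alike in both arms without reference to outcome, so that no student is dropped (for example, mean imputation for scores and a missing category for immigration background).

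The cost is a reordering of two analyses already planned, plus one sentence for the missing-value rule. No new data are needed. The small downside is that the headline result then depends on handling a few missing covariate values.

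### The named tests of the between-group difference at each timepoint, including the primary 6-month one, are post-hoc ANCOVAs with no stated class term, although classes are randomised and the primary model is a mixed model

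*Protocol article*

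**What the plan says.** All of the analysis wording is in the protocol article, Statistical analyses.

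- **Primary model.** "The primary ITT analyses will be performed using linear mixed models, which adequately deal with missing at random data". The nesting it is meant to handle is "students nested within classes and repeated assessments nested within students". Time, condition and their interaction are fixed effects, and the baseline score of the outcome is entered as well.
- **Effect sizes.** "Based on estimated marginal means and corresponding standard errors from linear mixed models, between-group effect sizes at each timepoint will additionally be expressed". The measure is Cohen's d, reported with a 95% interval.
- **Tests at each timepoint.** "Post-hoc tests will be conducted to examine between-group differences at each timepoint using analyses of covariance (ANCOVA), including baseline scores as covariate". Neither class nor the handling of missing outcomes is mentioned for these tests.

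Two other places bear on this. The abstract fixes the endpoint: "The primary outcome will be depressive symptoms using the Center for Epidemiologic Studies Depression Scale (CES-D) at 6-months follow-up". Design of the RCT fixes the unit of randomisation: "Participating classes will be randomly assigned to either the intervention or the control condition".

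**The concern.** The section says linear mixed models when it means them: for the primary analyses, for the effect sizes and for the moderator analyses. ANCOVA is named separately, with one covariate. An analyst following the text would fit a student-level ANCOVA at 3 months and another at 6 months, and would treat classmates as independent.

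The 6-month difference is the primary question. No coefficient or contrast of the mixed model is named as its test. The time-by-condition interaction asks whether the group difference changes over time, which is a different question. The only named test of the 6-month difference is therefore the ANCOVA, and its p-value is likely to be printed beside the primary result.

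Two things are at stake. A test that ignores class in a class-randomised trial rejects too often. And because d and its interval come from the mixed model, a p-value below 0.05 could stand next to an interval that includes zero, with nothing in the text to say which governs.

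**Working it through.** **Inputs** (protocol article, Sample size): mean class size 22; ICC 0.02; cluster-size variation 0.17, read as a coefficient of variation (CV); baseline correlation 0.30; d = 0.20; two-sided 5%; 80% power; 40% non-consent; 48 classes. The ICC sources cited there are a Dutch survey, 0.008 (95% CI 0.003 to 0.02), and a European study, 0.01 to 0.07. With 40% non-consent, the expected number analysed per class is 22 × 0.6 = 13.2, before any dropout.

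**The plan's own figures.** The plan gives no error rate for the ANCOVAs. Its nearest figures are 315 and 525 students.
- 315 / (1 − 0.40) = 525, as stated.
- The unadjusted, unclustered size is 2(1.960 + 0.842)² / 0.20² = 392.44 per condition. The design effect at 22 per class is 1.4327 (below). A factor of (1 + 0.30)/2 − 0.30² = 0.56, for the baseline-adjusted mean of two follow-ups with all correlations 0.30, gives 392.44 × 1.4327 × 0.56 = 314.9, that is 315.

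The two-follow-up reading is my inference; the article does not state it. It is used here only to show that 315 is consistent with a design effect of 1.43, so the plan's own sample size allows for clustering that the ANCOVAs do not mention.

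**Design effect.** DE = 1 + [(1 + CV²)m − 1] × ICC.
- m = 13.2: 1 + (1.0289 × 13.2 − 1) × 0.02 = 1.2516
- m = 22: 1 + (1.0289 × 22 − 1) × 0.02 = 1.4327

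The standard error of an analysis without class is too small by a factor of √DE, that is 1.12 or 1.20.

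**True type I error of a nominal 5% test** = 2[1 − Φ(1.96/√DE)]:

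| ICC | DE, m = 13.2 | true error | DE, m = 22 | true error |
|---|---|---|---|---|
| 0.003 | 1.038 | 5.4% | 1.065 | 5.8% |
| 0.008 | 1.101 | 6.2% | 1.173 | 7.0% |
| 0.02 | 1.252 | 8.0% | 1.433 | 10.2% |
| 0.07 | 1.881 | 15.3% | 2.515 | 21.7% |

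At ICC 0.02 a reported p of 0.03 corresponds to about 0.052 (m = 13.2) or 0.070 (m = 22).

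**Simulation check.** Student-level ANCOVA, 48 classes, all clustering at class level, correlation 0.30 between baseline and outcome at both class and student level, 10,000 runs per setting. At ICC 0.02 it rejected 8.3% (m = 13.2) and 9.7% (m = 22). A baseline-adjusted test on class means held 5.4% and 4.9% on the same data.

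**School level.** The article expects about four classes per school, divided across the conditions. Correlation shared by a whole school then largely cancels between arms. With 12 schools, two classes per arm in each, 13 students per class and a total ICC of 0.02, the simulated error of student-level ANCOVA was 7.7% with all clustering at class level, 6.5% to 6.8% (two runs) with half at school level, and 4.9% with all of it at school level. The documents do not give this split, so these are illustrations.

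**The case against.** The strongest reply is that this is not the trial's primary analysis. The ANCOVAs are labelled post-hoc. The primary intention-to-treat analysis is a mixed model chosen to handle nesting and data missing at random, and it already supplies an effect size with a 95% interval at 6 months. That stands. A reader might infer that the trial's main inference ignores clustering, and the documents do not support this. What remains is that no mixed-model contrast is named as the 6-month test, while the ANCOVA is.

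A second reply is that the article is condensed and does not rule out a class effect or robust errors in the ANCOVA. That is true, and the statement here is limited to the text as written. But the article names a method and its covariate, and the method is set apart from the mixed models, so this is more than a detail left for later.

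A third concerns missing outcomes. A reader might infer that the plan drops non-completers and gives up intention-to-treat. The text says neither: it applies the intention-to-treat principle to the analyses generally and is silent on missing outcomes in the ANCOVAs. A single-timepoint ANCOVA would probably use only students with that outcome and so lose the mixed model's handling of missing data. That would cost power and could bias the estimate, but it would not in itself make p-values too small. Only the missing class term does that.

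A fourth is size. The 15% to 22% figures need the top of the cited ICC range. At the Dutch survey ICC the error is 6% to 7%, and school-level clustering would lower it further. This limits the magnitude without removing the fault.

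**Conclusion.** The point holds in a limited form. The ANCOVAs, as written, test the difference at each timepoint, including the primary one, without a class term in a class-randomised trial. At the protocol's ICC of 0.02 the nominal 5% test has a true error of about 8% to 10%. Across the cited ICCs the range is from just over 5% to about 22%.

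These figures assume that the ANCOVA has no class adjustment of any kind, that all clustering is at class level, and that adjusting for baseline leaves the ICC unchanged. If part of the clustering is at school level the inflation is smaller, and it vanishes if all of it is.

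The p-value and the effect-size interval for the same 6-month contrast would come from different models and could conflict. The primary mixed model itself is sound on nesting and on data missing at random.

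**What to change.** Replace the ANCOVA sentence. State that the between-group differences at 3 and 6 months, with their confidence intervals and p-values, are contrasts from the same linear mixed model (class random effect, baseline covariate) that supplies the marginal means and Cohen's d, and that the 6-month contrast on the CES-D is the primary test. The choice of degrees of freedom can be left to the statistical analysis plan.

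If the ANCOVAs are kept as a supplementary check, say how class enters them, how missing outcomes are handled, and that the mixed-model contrast governs if the two disagree.

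The cost is one or two sentences before analysis. No data collection changes, and the contrasts come from a model already being fitted.
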